### **Secondary outcomes**

For physical activity, the Choi et al. (2011) algorithm will be used to define (non-)wear time. Next, the cutpoints of Barnett et al. (2016) will be used to determine time spent in moderate-to-vigorous physical activity.

Other outcomes will be processed as indicated in their corresponding manuals.

The same analysis as for the primary outcome will be used. The only difference will be the covariates: for physical activity these will be age and sex, for psychosocial wellbeing these will be age, sex and civil status.

The analysis will be conducted for the intention-to-treat and per protocol populations.

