## 3. Participants

### 3.1. Recruitment

Participants for this study will be recruited by convenience and snowball sampling. Flyers with basic information on the study, the researcher's contact information (i.e. e-mail address and phone number), and name of the study's website will be distributed through different channels. Examples of these channels are local service centres, community health centres, stakeholders and organisations for older adults (e.g. OKRA, Vief, S-plus, Vlaamse Ouderenraad), social media and mail to people who previously showed interest in this program and provided their contact details (e.g. people that were not selected for participation in the pilot study but agreed to be kept informed about this study, people reached through an information day (Care4Brain) of the Leuven Brain Institute). On the website, we will share a brief summary of what is expected of study participants. Furthermore, our in- and exclusion criteria as well as our contact information will be listed on the website. It will also be stated that during an initial phone call, the in- and exclusion criteria will be discussed and that only with participants meeting these criteria, an appointment will be made for the baseline measurement. We will also try to specifically reach neighbourhoods of people with lower socioeconomic status, because these people are often less physically active. We will do this by distributing our flyers in community (health) centres in person, to have

a first personal contact with our potential participants. Furthermore, an advertisement will be placed in a local newspaper and/or on Facebook and we will organize live information sessions for all those interested. To ensure the handed information is understandable for everyone, we will use no specialist terms on our flyers or website.

We will also recruit coaches, who will supervise the sessions. These coaches will be hired, and thus paid, for their contribution to this project. To recruit them, will contact Wandelsport Vlaanderen saying that we are looking for certified walking coaches for this particular project, including a flyer that can be distributed. They will then contact the suited walking initiators and let us know who is interested in this project. By certified, we mean that the coaches have completed the training 'walking initiator' of Wandelsport Vlaanderen and Vlaamse Trainersschool.

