### Baseline visit

First, the informed consent will be signed. At this moment, participants can also ask questions at the researcher if they have any after reading the information letter. During the baseline visit, the MoCA and BDI-II will be administered as a secondary screening for possible cognitive difficulties and depressive symptomatology, respectively. As mentioned above, participants excluded from the study at this stage will be informed about the deviant score by the either the PhD student or the postdoctoral researcher. Furthermore, the person will receive a letter that they can bring at their next appointment with their general practitioner. The letter will (1) contain the description of the test and the score obtained and an explanation that there are multiple possible reasons for such a score, and that only one of them is (mild) cognitive impairment or depressive symptomatology and (2)

indicate that, in case the general practitioner thinks this is necessary, an appointment can be made with a memory clinic or psychologist.

Included participants will be asked to provide sociodemographic information (i.e. age, gender, length, weight, nationality, country of origin, educational level, marital status, longest held profession, and income) during this baseline visit. Furthermore, participants will be asked if there is any relevant medical information the coaches need to know to ensure safety of the waling sessions (i.e., so the coach can anticipate any possibly dangerous situations).

Participants will also be asked to complete the questionnaires regarding cognitive function, psychosocial wellbeing, physical activity and general health described above (see *outcomes*). Objective cognitive and physical activity will be measured at baseline as well by administering the CANTAB and wearing an accelerometer for seven consecutive days (day + night), respectively. Participants will be asked to return the accelerometer by delivering it to the office of one of the researchers or by returning it by post (pre-paid by the research team).

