### 6.4. Statistical analyses

#### General

For descriptive statistics, categorical data will be presented as percentages and counts, continuous data will be presented as means with standard deviations or medians with interquartile range in case of non normally distributed data.

For inferential statistics,  $\alpha$  will be set at 0.05, and 95% confidence intervals will be calculated. In case of multiple testing, a correction of the p-values will be used.

Covariates will be specified below and are selected based on theoretical knowledge.

Checks of assumptions will be performed, in case of non-normality, transformations of the variables or non-parametric tests will be used.

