The outcomes are measured repeatedly at different time points, and are nested within individuals. This implies our data has a two-level structure, and this calls for an analysis technique taking into account the correlation between observations from the same person (Hoffman & Walters, 2022). Therefore, linear mixed models with random intercepts will be used, to take into account that each individual participant has a different starting point. Time (baseline, 3m, 6m and 12m) and condition (PA+CA, PA only, CG), and their interaction will be included as fixed effects.

Models with different levels of adjustment will be run: (1) crude model, (2) partially adjusted model including age, sex and education as covariates, and (3) fully adjusted model including age, sex, education, baseline PA and baseline CA as covariates. Model fit indices will be used to choose the models with the best fit.

In case of significant effects, post-hoc pairwise comparisons will be conducted to examine differences in the estimated marginal means of the outcome at T0, T1, T2 and T3 between 1) WALK+ vs. WALK-only and 2) WALK+ vs. CONT, but also the changes from T0 to T1, T0 to T2, T0 to T3, T1 to T2 and T2 to T3 for each group (WALK+, WALK-only and CONT). The p-values will be corrected for multiple testing.

The analysis will be conducted for the intention-to-treat and per protocol populations.

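### The physical-activity model omits educational level although the plan itself links socioeconomic status to activity; the cost is a small loss of precision, confined to the between-arm comparisons at single visits

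*Combined protocol and SAP*

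**What the plan says.** Section 6.4 (General) gives the rule for covariates: "Covariates will be specified below and are selected based on theoretical knowledge". Section 3.1 states a relevant piece of such knowledge when it explains why the team will try to recruit in "neighbourhoods of people with lower socioeconomic status, because these people are often less physically active". The baseline visit in section 5.3 records "educational level, marital status, longest held profession, and income", and section 2 has allocation disclosed only once baseline measurements are complete, so these are proper baseline variables.

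For cognition, the Primary outcome text in section 6.4 has a "partially adjusted model including age, sex and education as covariates", and the fully adjusted model keeps education. For the secondary outcomes, "The same analysis as for the primary outcome will be used" apart from the covariates, and "for physical activity these will be age and sex". Psychosocial wellbeing gets civil status as a third covariate. No reason is given for leaving education out of the activity model.

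The inherited model has time (four visits, baseline included), condition and their interaction as fixed effects: "linear mixed models with random intercepts will be used, to take into account that each individual participant has a different starting point". If effects are significant, the named between-arm comparisons are of estimated marginal means at T0, T1, T2 and T3 (WALK+ against WALK-only, and WALK+ against CONT). The changes over time that are listed are within each group. Section 6.1 hypothesises that both walking arms do better than control on MVPA.

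**The concern.** The only link between socioeconomic status and an outcome that the plan states concerns physical activity. By the plan's own rule, a socioeconomic marker is a natural candidate for that model. Education is to hand and is used for cognition, but is missing from the model to which the stated link applies.

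At stake is precision. A comparison of two arm means at one visit carries all the between-person variance that the covariates do not explain. Randomisation is stratified by location and scheduling option only (section 2), so education can differ between arms by chance, and part of that difference passes into a single-visit comparison. Section 6.4 tests baseline differences but states no action if one is found. Naming the covariate in advance removes any temptation to add it afterwards.

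**Working it through.** **Figures in the plan.** The plan gives no power or precision figure for physical activity, so there is none to reproduce. The sample size in section 6.2 (124, raised to 149) concerns the main comparison of conditions and enters here only as arm sizes: 149/3 ≈ 50 recruited and 124/3 ≈ 41 remaining per arm.

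**Assumptions, not in the documents.** R² is the share of total MVPA variance that education explains beyond age and sex: 2%, 5% or 10%. ICC is the correlation between repeated MVPA measurements in one person: 0.5 to 0.8. MVPA is scaled to SD 1, and education enters as a main effect.

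**Step 1: change from baseline, and hence the interaction.** With complete data, the difference between two arms in change from baseline has

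SE = √[(2/50) × 2 × (1 − ICC)].

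At ICC = 0.7 this is √(0.04 × 0.6) = 0.1549. Only within-person variance appears. Education does not vary within a person, so adding it leaves 0.1549 unchanged (0.00%). With 20% of participants dropping out, generalised-least-squares standard errors for the planned model fall by at most 0.13% over the whole range.

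**Step 2: one visit.** With complete data and no education term,

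SE = √(2/50) = 0.2000.

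If the covariate's slope were known, the SE would be 0.2000 × √(1 − R²); at R² = 5% that is 0.2000 × 0.975 = 0.1949. Estimating the slope costs a little, and the planned model at ICC = 0.7 gives 0.1955, a fall of 2.3%. Over ICC 0.5 to 0.8, with complete data and with 20% dropout:

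| R² beyond age and sex | Fall in SE, single-visit comparison | Fall in SE, change from baseline |
|---|---|---|
| 2% | 0.7-0.8% | 0.00% complete; at most 0.02% with dropout |
| 5% | 2.1-2.3% | 0.00% complete; at most 0.06% with dropout |
| 10% | 4.6-4.9% | 0.00% complete; at most 0.13% with dropout |

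**Step 3: what this means for power.** Take a single-visit comparison with 41 per arm and a true difference that gives 80% power without education (0.62 SD, normal approximation). Multiplying the SD by √(1 − R²) raises power to 80.8%, 82.0% or 84.0%. These are slightly generous, because they ignore the cost of estimating the slope.

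**Step 4: chance imbalance.** With 50 per arm, the shift in an unadjusted single-visit comparison caused by imbalance in education has SD √(2/50) × √R² = 0.028, 0.045 or 0.063 of an MVPA SD. Multiplied by 1.96, that is 0.055, 0.088 or 0.124, exceeded in about 1 trial in 20. This is the same loss as in step 2 seen from another side, so the two must not be added. A stable shift of this kind is also present at baseline and drops out of the changes in step 1.

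**The case against.** The strongest reply is that the hypothesis of a more beneficial effect on MVPA is tested by the time-by-condition interaction, and that the visit means are compared only after a significant effect. For the interaction the omission costs nothing. That stands. A reader might infer that the activity analysis as a whole is less precise than it need be; the model in section 6.4 does not support that. What remains is that the only between-arm comparisons the plan names are those at single visits, and they would be reported as the estimates of effect.

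It is also fair to say that a short covariate list is legitimate, that theoretical knowledge does not oblige the team to include every recorded correlate, and that the gain is small and rests on an assumed R². All of that stands, and it limits the point to a refinement.

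Three further inferences are tempting and should not be drawn.

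- **Wider socioeconomic spread.** Section 3.1 says only that the team will try to reach these neighbourhoods, within convenience and snowball sampling. The spread achieved is unknown.
- **Missing data.** Nothing in the documents suggests that dropout depends on education, and the likelihood-based model already conditions on each person's observed activity.
- **IPAQ-SF.** Section 5.1 describes its score as categorical, so standard-error arithmetic from a linear model does not carry over.

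Finally, the plan gives no coding for education and lets fit indices choose among adjustment levels, so naming the covariate does not by itself guarantee that it is in the reported model. Both remarks are correct and bear on how the fix is worded.

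**Conclusion.** The point holds in a narrow form. Leaving educational level out of the MVPA model sits poorly with the plan's own covariate rule, its statement about socioeconomic status and activity, and its use of education for cognition. It is not a contradiction between passages. It introduces no bias under randomisation and leaves the interaction and change-from-baseline results practically untouched. The loss is confined to the between-arm comparisons of MVPA means at each visit: roughly 1%, 2% or 5% of the standard error if education explains 2%, 5% or 10% of MVPA variance beyond age and sex. Those percentages are assumptions; if the true share is near zero, so is the gain. The point is minor, and worth acting on only because the change is so cheap.

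**What to change.** In section 6.4, Secondary outcomes, list the covariates for accelerometer MVPA as age, sex and educational level. Define the coding of education once and use it in both the cognition and the MVPA models. If selection by fit indices is meant to apply to this outcome too, say whether the named covariates stay in the reported model regardless. If the team prefers to leave education out, one sentence giving the reason would settle the matter.

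The cost is a phrase in the SAP and one or two extra model parameters. No new data are needed, since educational level is already collected for every included participant.

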### **Process evaluation**

Quantitative data from the questionnaires will be handled in SPSS IBM Corp (2021). Descriptive statistics (frequencies, percentages, median and range or mean and standard deviations) of the responses to the questions will be generated.

Audio-recordings of the focus groups will be transcribed verbatim. A thematic analysis will be conducted on the transcripts of the focus groups and the data from the open-ended questions of the questionnaire data in the qualitative data management software Nvivo (QRS International Pty Ltd, 2022), in order to gain insight in the most important themes of the implementation of the intervention. Data will first be coded deductively (top-

down, data-driven) using the framework of Saunders et al. (2005), and additionally inductively (bottom-up, data-driven).

### Baseline differences

Conditions will be compared on baseline sociodemographic characteristics and outcome measures, using one-way ANOVA's for normally distributed continuous data, Kruskal-Wallis tests for non-normally distributed continuous data and ordinal data, and Chi-square tests for nominal data.

